**(6) Ultrasound examination of carotid plaques**

Ultrasonography of carotid plaques includes their location, size (length × width), and morphology as well as the intima-media thickness (IMT) and Crouse’s score of the common carotid artery.

A certified sonographer proficient in examining the carotid arteries will perform ultrasound evaluations at multiple time points: at baseline (24th hour post PCI); on the 5th and 10th days; and at the end of the 1st and 3rd months post intervention.

**(7) Six-minute walk test**

The six-minute walk test (6MWT) quantifies the maximal distance an individual can walk in 6 minutes, serving as an indicator of the patient's exercise capacity and cardiorespiratory fitness during routine physical activities.

A certified cardiologist will conduct the 6MWT at various time points, including at enrollment, on the10th day, and at the end of the 1st and 3rd months post intervention.

**(8) Short-term heart rate variability**

HRV refers to the fluctuation in the timing of consecutive heartbeats or the variance in heart rate. It is determined by the duration between two successive R-R intervals, representing the slight deviation between each cardiac cycle. HRV assessment will be conducted using the amor HRV Guard Analyzer (ZSY-1, Taiwan, China). With the patient at rest and in a supine position, short-term (5-minute) HRV will be measured during daytime hours.

Certified cardiologists will perform short-term HRV assessments at baseline (24th hour post PCI), on the 5th and 10th days, and at the end of the 1st and 3rd months post intervention.

**(9) Tools for mental health assessment**

The Patient Health Questionnaire-9 (PHQ-9) is a critical instrument for the screening, diagnosis, and assessment of depression, enabling the measurement of its severity. Concurrently, the 7-item Generalized Anxiety Disorder Scale (GAD-7) enables the evaluation of generalized anxiety disorder. Similarly, the Pittsburgh Sleep Quality Index (PSQI) stands as a widely recognized assessment tool for determining sleep quality, and the Seattle Angina Questionnaire (SAQ) functions as a self-administered assessment tool designed to evaluate specific functional status and quality of life among individuals with CAD.

Mental health assessments will be conducted by certified psychologists at various time points: at baseline (24th hour post PCI), on the 10th day, and at the end of the 1st and 3rd months post intervention.

**4** **Statistical analysis**

The baseline characteristics of both groups will be summarized using appropriate descriptive statistics. Analysis of both primary and secondary outcomes will be based on the intention-to-treat approach, ensuring that all participants remain assigned to their original group throughout the study.

Normally distributed data will be presented as the mean (standard deviation), and non–normally distributed data will be depicted as the median (interquartile range). Group comparisons will be conducted using independent sample tests, and within-group comparisons before and after treatment will be evaluated using paired sample tests. Clinical symptom variables will be portrayed as percentages. Categorical data will be assessed using either the chi-squared test or Fisher’s exact test. A significance level of.05 will be employed to interpret the P values. The statistical analysis will be conducted utilizing SPSS version 26 statistical software (IBM, Armonk, NY).

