**Summary of Study Protocol**

| **Project Name** | A study protocol of the rehabilitative efficacy of cardiovascular ultrasound therapy after percutaneous coronary intervention in patients with coronary artery disease: A multicenter, parallel-group, randomized controlled study |
| --- | --- |
| **Objective** | The aim of this study is intended to evaluate the rehabilitative efficacy of cardiovascular ultrasound therapy in patients with coronary artery disease (CAD) who had already undergone percutaneous coronary intervention (PCI). Specifically, the study aims to examine the effects of cardiovascular ultrasound therapy on inflammatory markers, serum lipids, endothelial function, cardiac function, carotid artery plaque, and hemodynamics. In addition, the study will analyze patients’ heart rate variability (HRV), record their symptoms, and score depression and anxiety. |
| **Research Hypothesis** | Cardiovascular ultrasound therapy has the potential to reduce perioperative myocardial damage, reduce the production of inflammatory factors and inflammatory cells, and has a certain regulatory effect on blood lipids, platelet function, hemodynamics and blood pressure in patients after PCI. |
| **Study Design** | This study is a multicenter, parallel-group, randomized controlled clinical trial. Subjects were enrolled by randomization into groups of 20 per center, with 10 in the control group and 10 in the treatment group. Each participating unit completes the relevant content of the subject case list. |

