**Detailed study of the reference frame of the program**

**1 Introduction**

Coronary artery disease (CAD) is caused by atherosclerotic lesions in the coronary arteries, resulting in narrowing or blockage of the lumens of the vessels; this, in turn, causes myocardial ischemia, hypoxia, and necrosis ^[1]^. CAD has a high rate of morbidity and mortality and poses a severe threat to human health ^[2]^. Percutaneous coronary intervention (PCI) uses cardiac catheterization to improve myocardial perfusion by unblocking narrowed or occluded coronary arteries ^[3]^. As the least invasive revascularization procedure available, PCI has become the mainstay of treatment for CAD ^[4]^. However, as an invasive test and treatment method, it is often accompanied by a variety of postprocedural complications, including in-stent thrombosis or restenosis, no or slow reflow, arrhythmia, and an inflammatory response, which can significantly affect a patient’s condition and prognosis ^[5]^. Treatments for common complications after PCI include pharmacologic therapy, interventional repeat angioplasty, or stent implantation ^[5]^. However, medication can also lead to adverse effects, and such interventions as well as surgery are risky and costly ^[6]^. Therefore, there is new interest in the exploration of noninvasive, low-side-effect treatments to prevent postoperative complications and promote cardiac rehabilitation after PCI.

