**3.4 Calculation of sample size**

Our calculations of sample size and power are based on the primary outcomes, utilizing a two-sided analysis with a statistical power of 90 % (1 – β = 0.90) and a significance level of α = 0.05. Owing to the lack of prior studies examining cardiovascular ultrasound therapy following PCI, the sample size was determined following an extensive evaluation by a panel of experts. Targeting long-term inflammation and cardiovascular efficacy, they selected high-sensitivity C-reactive protein (hsCRP) as the primary biomarker, given its relevance and the larger sample size required by interleukin 6.

Cardiovascular ultrasound is estimated to reduce hsCRP levels by an average of 4 mg/L. To meet this target, 160 participants (80 per group in a 1:1 allocation) are projected to be needed. Factoring in an anticipated dropout rate of 20 %, the final sample size would be adjusted to 200 participants (100 per group), ensuring adequate statistical power and robustness for the study’s objectives.

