**3.9 Outcomes**

**3.9.1 Primary outcome**

The primary outcome measures will focus on the levels of hsCRP and interleukin-6 in the peripheral serum following 20 cardiovascular ultrasound therapy sessions (i.e., on the 10th day). Comparative analyses will be conducted between the cardiovascular ultrasound therapy intervention and control groups along with pre- and postintervention assessments.

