**(3) Serum inflammatory factors**

Each morning, 5 mL of fasting venous blood will be drawn by nursing staff to assess the proportion of inflammatory cells and measure levels of inflammatory markers in the peripheral blood.

Monitoring of serum inflammatory factors will be conducted at baseline (24th hour post PCI), on the 10th day, and at the end of the 1st and 3rd months post intervention.

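### The randomised contrast is not made decisive for the primary outcome: unadjusted between-arm tests forgo the baseline values, and within-arm paired tests that cannot show efficacy stand beside them

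*Protocol*

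**What the plan says.** Section 4 (Statistical analysis) sets the method for primary and secondary outcomes alike: "Group comparisons will be conducted using independent sample tests, and within-group comparisons before and after treatment will be evaluated using paired sample tests". It applies a significance level of .05 to the P values without distinguishing the two kinds of test. No covariate, centre term or regression model appears anywhere in the protocol.

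Section 3.9.1 defines the primary outcome as hsCRP and IL-6 on day 10 and continues: "Comparative analyses will be conducted between the cardiovascular ultrasound therapy intervention and control groups along with pre- and postintervention assessments". It does not rank the two comparisons.

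A baseline for the inflammatory markers is available. Section 3.9.2 (3) reads: "Monitoring of serum inflammatory factors will be conducted at baseline (24th hour post PCI), on the 10th day". The Introduction lists, among the complications that often accompany PCI, "arrhythmia, and an inflammatory response".

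The Study Design row of the Summary describes "groups of 20 per center, with 10 in the control group and 10 in the treatment group". Section 3.5 (Randomization and blinding) does not mention stratification by centre.

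**The concern.** There are two separate problems.

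**Precision.** Baseline values of both primary markers will be on file. A two-sample test of day-10 levels leaves unused whatever they explain of the day-10 values. This costs power but causes no bias.

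**Interpretation.** Baseline is drawn 24 hours after a procedure that the protocol itself links to inflammation, so some fall in hsCRP and IL-6 by day 10 is plausible in both arms without any treatment. A paired test within the ultrasound arm cannot separate that fall from a device effect. Nor does a significant fall in one arm and a non-significant fall in the other compare the arms. Because sections 3.9.1 and 4 give these tests the same .05 level and a place under the primary outcome, a report could present either pattern as support for efficacy and still follow the plan.

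**Working it through.** **Inputs from the protocol (section 3.4).** Difference in hsCRP of 4 mg/L; 80 evaluable per arm; "a two-sided analysis with a statistical power of 90 % (1 – β = 0.90) and a significance level of α = 0.05".

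**Inputs not in the protocol (assumptions).** The SD of hsCRP; the correlation ρ between baseline and day 10; the size of any spontaneous fall. Values are approximately normal with equal SD at both times.

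**1. The plan's own figure.** With no SD stated, 80 per arm cannot be reproduced independently; it can only be solved backwards.
- Normal approximation: SD = 4 / [(1.960 + 1.282) × √(2/80)] = 7.80 mg/L.
- Noncentral t: SD = 7.76 mg/L, a standardised effect of 4/7.76 = 0.516.

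The steps below use 7.76 unless stated. The unadjusted power of 90% is then true by construction.

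**2. Baseline adjustment.** ANCOVA multiplies the residual variance by 1 − ρ². The noncentrality is 4 / [SD × √(1 − ρ²) × √(2/80)].

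| ρ | 1 − ρ² | Residual SD (mg/L) | Power, unadjusted | Power, ANCOVA | Power, change scores |
|---|---|---|---|---|---|
| 0.3 | 0.91 | 7.40 | 90.0% | 92.5% | 78.2% |
| 0.5 | 0.75 | 6.72 | 90.0% | 96.3% | 90.0% |
| 0.7 | 0.51 | 5.54 | 90.0% | 99.5% | 98.7% |

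The last column is included because section 4 does not say whether the independent-sample test compares day-10 levels or changes. Change scores have SD 7.76 × √[2(1 − ρ)] and give less power than ANCOVA in every row.

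If the true SD were 10 mg/L (normal approximation), unadjusted power would be 71.6%, against 75.6%, 83.2% or 94.3% with ANCOVA at the same three correlations.

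**3. Centre.** With balance within centre and an assumed intraclass correlation of 0.02 to 0.10 (SD 7.75, normal approximation), leaving centre out lowers the true type I error from 0.050 to between 0.048 and 0.039. Power is 90.6% to 91.5% unadjusted and 90.9% to 93.1% adjusted, a gain of about 0.3 to 1.5 percentage points.

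**4. Paired test in the ultrasound arm when the device does nothing.** The SD of the change at ρ = 0.5 is 7.76 × √[2(1 − 0.5)] = 7.76 mg/L. For a spontaneous fall m in both arms, the noncentrality is m / (7.76/√80), with 79 degrees of freedom. Let p be the probability of a significant fall. The arms are independent, so significance with ultrasound but not in control has probability p(1 − p).

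| Spontaneous fall (mg/L) | Noncentrality | p, ultrasound arm | Ultrasound only, p(1 − p) |
|---|---|---|---|
| 1 | 1.15 | 21% | 16% |
| 2 | 2.31 | 62% | 23% |
| 3 | 3.46 | 93% | 7% |
| 4 | 4.61 | 99.5% | 0.5% |

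In 20,000 simulated trials per setting (falls of 0, 1, 2 and 4 mg/L), the between-arm t-test rejected in 5.0% to 5.2%, whatever the spontaneous fall.

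**The case against.** The strongest defence is that the protocol does plan the right comparison. Section 3.9.1 names the between-arm analysis first, section 3.7.1 asks whether ultrasound does better than standard therapy, and section 3.4 sizes the trial as two groups. A reader might infer that efficacy will be judged by before/after change and that recovery after PCI will therefore pass for benefit. The documents do not support that. Recovery cancels in the planned randomised contrast, whose type I error stays at about 5%. What stands is narrower: nothing makes that contrast the only basis for a claim, and the paired tests carry P values under the same outcome.

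A reader might also infer a data-driven choice between t-test and rank test. Section 4 links normality only to how data are presented and states no such rule.

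The power figures are open to challenge too. The SD is back-solved and the correlation assumed, so the gain is certain in direction but not in size. In a log-normal model with control mean 8 mg/L, SD 7.76 and log-scale correlation 0.5, a 4 mg/L difference gives more than 99% power with or without adjustment. This is forgone precision, not a shortfall against the plan.

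Finally, where the paired test misleads most, the control arm will nearly always show a significant fall as well, which would expose the artefact. That is true at 4 mg/L, where the one-arm-only pattern has probability 0.5%, but much less so at 1 or 2 mg/L, where it has probability 16% or 23%.

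Covariates and scale are often left to a statistical analysis plan. Here, however, the protocol itself fixes the type of test, so a later plan would have to override it.

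**Conclusion.** The point holds as one of efficiency and interpretation and should be fixed; it is not an error that invalidates the trial. The planned between-arm test is valid but forgoes precision. At the implied SD of about 7.8 mg/L, baseline adjustment adds 2.5, 6.3 or 9.5 percentage points of power at correlations of 0.3, 0.5 or 0.7. It would also give some protection if the unstated SD proved larger. The within-arm tests are no evidence of efficacy at any sample size. Their error rates in the working depend on the assumed SD, correlation and spontaneous fall, but the logical fault does not. The centre element is minor and rests on the Summary alone.

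**What to change.** Replace the sentence on tests in section 4, and align section 3.9.1 with it, so that the protocol states:

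- The sole basis for efficacy is the between-arm difference at day 10, from ANCOVA on arm and the baseline value of the same marker, with a 95% confidence interval, for hsCRP and IL-6 alike.
- Centre is included as a factor if randomisation is balanced 10/10 within centre as the Summary says. Section 3.5 should confirm whether it is.
- The scale is fixed before outcome data are examined: either mg/L, which matches the 4 mg/L target in section 3.4, or log, with that target restated as a ratio of geometric means.
- Within-arm changes are shown descriptively, without P values.

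The cost is about one paragraph of wording, with no new data, visits or patients. If the log scale is chosen, the effect is reported as a ratio rather than in mg/L, and the sample-size target must be re-expressed to match.

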**(4) Hemodynamic parameters**

These encompass a comprehensive range of indicators, including cardiac index (CI), cardiac output (CO), stroke volume (SV), stroke volume index (SVI), mean arterial pressure (MAP), stroke systemic vascular resistance index (SSVRI), left ventricular stroke work index (LVSWI), systemic vascular resistance index (SVRI), ejection phase contraction index (EPCI), inotropic state index (ISI), systemic vascular resistance (SVR), vascular resistance (VR), and mean heart rate (mHR).

Certified sonographers will monitor hemodynamic parameters at baseline (24th hour post PCI); on the 5th and 10th days; and at the end of the 1st and 3rd months post intervention.

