**4.3 Analytic methods for handling protocol nonadherence and statistical methods for handling missing data**

We anticipate minimal missing data (<10%) for the primary outcome given that all participants will be in patients with regular daily contact maintained during treatment. The evaluation of missing data effects will involve comparing differences under plausible and extreme missing data scenarios. In the event of a significant primary test result, we will also assess the interaction size between group assignment and missing data necessary to render the difference nonsignificant. Should 10% or more of the baseline samples be excluded due to missing data, we will apply multiple imputation techniques for comprehensive analysis.

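### Secondary outcomes with three or four follow-up visits are compared by unadjusted two-sample tests read at .05: about 140 possible tests, about 7 expected false positives under no effect, and baseline unused

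*Protocol*

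**What the plan says.** Protocol section 4 gives one method for primary and secondary outcomes: "Group comparisons will be conducted using independent sample tests". Within each arm, "within-group comparisons before and after treatment will be evaluated using paired sample tests". The threshold is general: "A significance level of.05 will be employed to interpret the P values". The section names no longitudinal model, baseline or centre adjustment, leading secondary outcome or exploratory label. It does state intention-to-treat for both primary and secondary outcomes.

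Section 3.9.2 schedules repeated measurements. Hemodynamic parameters, for example, are taken at baseline and "on the 5th and 10th days; and at the end of the 1st and 3rd months post intervention". Other domains omit day 5 and have three post-baseline visits. The Summary (Study Design) sets 20 patients per centre, 10 in each arm.

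On missing data, section 4.3 says "We anticipate minimal missing data (<10%) for the primary outcome" and gives daily inpatient contact during treatment as the reason. It plans plausible and extreme scenarios, and multiple imputation once 10% or more of the baseline samples are excluded for missing data. Section 3.4 allows for 20% dropout.

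**The concern.** A two-sample test takes one value per patient. Applied to an outcome measured at three or four follow-up visits, it invites a separate test at each visit, each read at .05, with no stated rule on which one counts. With this many variables, several nominally significant differences are to be expected even if the therapy does nothing. Section 2 lists lipids, endothelial function, cardiac function, carotid plaque and hemodynamics among the things to be examined, so these P values will be read. Section 3.5 masks only those who collect primary outcome data, so the secondary outcomes lack that stated protection.

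The method also discards information already being collected: the baseline value of each outcome, and the centre within which allocation is balanced.

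The missing-data plan is written around the inpatient primary outcome at day 10. Its expectation of under 10% does not carry over to months 1 and 3, which fall after the 10-day treatment course. The imputation trigger names no visit or outcome, and below it the plain tests stand alone. Sections 3.3 and 3.7.2 provide for withdrawal after stopping treatment or clinical change, and for exclusion after drug changes that affect results. Missingness related to earlier values is therefore plausible.

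**Working it through.** **Plan's own figures.** The protocol gives no count of secondary tests, so there is none to reproduce. Its dropout step does reproduce: 160 / (1 − 0.20) = 200.

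**Count of tests.** Variables and post-baseline visits, from section 3.9.2:

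| Domain | Variables | Visits | Tests |
|---|---|---|---|
| Myocardial injury | 3 | 3 | 9 |
| Lipids | 8 | 3 (assumed) | 24 |
| Endothelial markers | 3 | 4 | 12 |
| Hemodynamics | 13 | 4 | 52 |
| Echocardiography | 3 | 4 | 12 |
| Carotid (size, IMT, Crouse) | 3 | 4 | 12 |
| 6MWT | 1 | 3 | 3 |
| HRV | 1 (minimum) | 4 | 4 |
| PHQ-9, GAD-7, PSQI, SAQ | 4 | 3 | 12 |
| **Total** | **39** | | **140** |

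Equivalently, 16 × 3 + 23 × 4 = 140. The schedule sentence under item (1) names only the injury markers; the same visits are assumed for lipids. HRV indices and the inflammatory factors of item (3) are not itemised, so 39 is close to a minimum.

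**Expected false positives under no effect** = tests × 0.05. Correlation does not change this mean.

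- Main count: 140 × 0.05 = 7.0
- Lipids omitted: 116 × 0.05 = 5.8
- Lipids at day 10 only: 124 × 0.05 = 6.2
- All five carotid items: 148 × 0.05 = 7.4
- All five carotid items plus two assumed inflammatory variables at three visits: 154 × 0.05 = 7.7
- One test per variable: 39 × 0.05 = 1.95

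Paired tests in both arms at every visit would add 2 × 140 = 280 more; they are not in these figures.

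**Chance of at least one false positive among 140.** This does depend on correlation. With independence it is 1 − 0.95^140 = 0.999. Simulation under assumed correlations (between outcomes / between visits of one outcome) gives:

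- 0 / 0.6: 0.996
- 0.2 / 0.6: about 0.987
- 0.4 / 0.7: 0.91
- 0.5 / 0.8: 0.81, with a median of 3 false positives although the mean stays at 7

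**Precision.** Against a test of the follow-up value alone, baseline adjustment multiplies variance by 1 − r², where r is the baseline to follow-up correlation. The protocol gives no r, so a range is assumed:

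- r = 0.3: 0.91 (9% lower)
- r = 0.5: 0.75 (25% lower)
- r = 0.7: 0.51 (49% lower)

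If the two-sample test were applied to change from baseline, its variance factor would be 2(1 − r). The ratio is then (1 − r²) / [2(1 − r)] = (1 + r)/2, that is 0.65, 0.75 and 0.85 for the same r. Adjustment is more precise than either form of the simple test.

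**Missing data.** The allowance in section 3.4 is 20%; the imputation trigger in section 4.3 is 10%. Loss at the planned rate would meet the trigger, if the trigger is read as applying to that visit and outcome. The text does not say so.

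**The case against.** The strongest reply is that much of this belongs in a statistical analysis plan, which is not shown, and that unadjusted secondary outcomes are common and acceptable when nobody treats them as confirmatory. That stands as far as an absent covariance structure or contrast list goes. It does not remove the point, because section 4 itself fixes the test family and the threshold for secondary outcomes.

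The 140 tests are inferred. Section 4 never says that every visit is tested, and one change score per outcome would fit its wording and give about 2 expected false positives. That also stands, and the conclusion is conditional on it. Several hemodynamic variables are near-duplicates (CO and CI, SV and SVI, SVR and SVRI), so false positives would cluster, and calling at least one almost certain would overstate it.

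A reader might infer that dropout at months 1 and 3 is ignored, or that only completers are analysed. The documents do not support this. Section 4 states intention-to-treat for secondary outcomes, section 4.3 plans scenario analyses and imputation, and section 3.4 allows for 20% dropout. A reader might also infer that the protocol claims effects on lipids, plaque and the rest; section 2 only sets out to examine them. Finally, "Targeting long-term inflammation and cardiovascular efficacy" in section 3.4 explains the choice of hsCRP. Section 3.9.1 fixes the primary time at day 10, so the phrase does not make months 1 and 3 a confirmatory target.

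It is also fair to say that a mixed model does not in itself reduce the number of contrasts.

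**Conclusion.** The point holds in limited form, as an inexpensive improvement that should be made. The stated method for secondary outcomes is an unadjusted two-sample test read at .05, although most of these outcomes have a baseline and three or four follow-up values and allocation is balanced within centre.

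If each post-baseline visit is tested, about 7 false positives are expected under no effect on any outcome (5.8 to 7.7 by counting choice); with one test per outcome, about 2. The loss of precision against a follow-up-only test is 25% of the variance at an assumed correlation of 0.5, and 9% to 49% over 0.3 to 0.7.

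On missing data the conclusion is narrow: a plan exists, but its under-10% expectation rests on inpatient contact for the primary outcome, and its 10% trigger is not tied to the month 1 and 3 visits.

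**What to change.** Amend section 4 as follows.

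- Analyse each continuous secondary and follow-up outcome with one repeated-measures mixed model: arm, visit, arm × visit, baseline × visit and centre, on the log scale for skewed markers.
- Name in advance one between-arm contrast per outcome, at the visit suited to that outcome. Report the other visits as estimates with 95% CI.
- State that secondary P values are nominal and exploratory and are not grounds for an efficacy claim.
- Keep the scenario analyses and multiple imputation of section 4.3 as sensitivity analyses, and tie them explicitly to months 1 and 3. Imputation also brings in randomised patients with no follow-up value, whom the mixed model leaves out.

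The parts do different work. The single contrast and the nominal label deal with multiplicity, cutting 140 tests to 39. The model deals with precision and with missingness that depends on observed values, without a switch at 10%.

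No visit, sample or procedure changes, and SPSS 26, which the protocol names, can fit the model. The cost is analysis work, the choice of a covariance structure, and fewer nominally significant secondary results to report.
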